**STATISTIC ANALYSIS**

The lack of literature on precise estimate of the effect (effect size) of the manual treatment with osteopathic modality on the main outcome limits the calculation of the sample size. Therefore, given the lack of research measuring these effects at the brain level using fMRI, it is rather difficult to have a precise effect-size estimation. However, in general, the estimates reported in the literature for the expected effect-size with fMRI measures (eg comparison of connectivity values between different populations as in Greicius et al., 2007) indicate relatively high values (Cohen ‘s d= 1.01). This effect-size, together with an alpha and beta value of 0.05 and 0.8 respectively as usual in neuroimaging studies (Desmond et al., 2002) have been included in the R Statistical program to estimate the sample size, resulting in N=16 subjects per group.

Statistical analysis will be based on the 'intention-to-treat' and 'per-protocol' method. The statistical analysis will use the mean and standard deviation, median and percentiles, percentage points for the description of the variables of the two groups. The analyzes will be standardized by age and gender. The hypothesis H0 (null hypothesis) is the non-difference between the two groups at the end of the treatment. To test this hypothesis the assumption of the normal distribution of data through the Shapiro test will be tested first.

The analysis of residuals indicates the possible use of logarithmic transformations of the data. Subsequently the univariate analysis foresees the use of the analysis of the variance (ANOVA) for the comparison of the numerical variables, while the chi square (chi-square test) for the categorical and / or ordinal variables. Primarily used for the comparison of the two samples to the baseline, with the same method we will also analyze the data at the end of the treatment taking into account the inability to detect the independent effect of the variables on the outcome. ANCOVA will be used to explore in greater detail the treatment effect considering cofactors. Multivariate analysis will include the use of the best weighed model for confounding and interaction factors.

The level of statistical significance is established for an alpha <0.05. A post-hoc power calculation will be carried out.

Table 1. Exclusion criteria

• Subjects in acute phase,

• Subjects aged under 30 and over 50

• Associated co-morbidities (i.e. metabolic syndrome)

• Subjects with previous surgical operations,

• Subjects with congenital anomalies,

• Cardio-vascular, respiratory, gastro-enteric diseases,

• Pregnant women,

• Subjects with chronic pain> 10 years

• Subjects with psychiatric illness or overt psychic disorders

• Subjects with vertigo syndrome

• Subjects with associated cervicalgia

• Obese subjects

• Diabetic subjects

• Subjects in pharmacology

• Subjects without a history of drug or alcohol abuse

• Subjects under physiotherapy

• Subjects with experience of manual treatments with osteopathic modality

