
The correlations between the various brain areas appear to be exclusive. In fact, the individual structures of each network seem to be anti-correlated. This reinforces the idea that the two portions of the insula underlie different functions and are connected to different networks that work independently [17].

One way to measure the functional connections between the various brain areas is during the "resting state" condition, in which the subject is in the absence of stimuli. Fluctuations of brain activity are recorded using fMRI with BOLD technique [18]. This allows to highlight spontaneous activity patterns known as resting state networks (RSN) [13, 17, 19, 20]. The properties of the BOLD signal of the RSN seem to be consistent between individuals and stable between different measurement sessions [21-23]. The SN and therefore the insula circuits have also been studied in the field of RSN, with more precise areas of brain involvement [11, 12]. Menon and Uddin have hypothesized that the right anterior insula acts as a causal center of efference that coordinates two important networks of executive (external, posterior insula) and interoceptive (internal, anterior insula) control [11]. Thus the connection hypotheses formulated by Craig [1-3, 24] as well as the SN [11, 12] define the role of the right insular cortex as a pivotal region in the brain's attentive system [25, 26].

Moreover, some authors have studied the activation of the insula cortex in relation to specific tasks: interoceptive (heartbeat [27] or breath [28]) and exteroceptive [29], showing significantly different behaviors.

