**STUDY / CONTROL GROUP**

*Randomization*

All patients included in the study are registered with a progressive identifier (patient code). The treatment arm will be assigned by random selection procedure. A computerized randomization algorithm based on the binomial distribution constructs a balanced and progressive list of random values ​​assigned within a specific interval (in this case 1 = group A, 0 = group B), this is also called randomization code. A progressive index is associated with each value. Treatment is assigned by assigning to each patient the randomization code relative to the equivalent patient code.

The randomization process will be based on the use of a software for randomization (R statistical software) [45] and conducted by a "permuted block" ratio of 1: 1.

The study foresees two groups (one of study and one of control) of 20 subjects each (= figure 1). The study group (OMT) will consist of 20 subjects who will receive osteopathic manipulative treatment. The sham control group will receive a similar touch without any technique.

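### Ordinal variables are assigned to the chi-square test, which ignores category order and loses power at 20 per arm; a rank or proportional-odds test is a free improvement

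*Protocol*

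**What the plan says.** The protocol's Statistic Analysis section first tests normality with the Shapiro test and then adds: "The analysis of residuals indicates the possible use of logarithmic transformations of the data". It does not say which variables this concerns. Univariate comparisons follow: ANOVA for numerical variables, "while the chi square (chi-square test) for the categorical and / or ordinal variables". The section describes this mainly as a baseline comparison but says the same method will also be applied to end-of-treatment data. No rank test and no exact test is named.

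Three other places bear on the point:

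- **Group size.** The Study / Control Group section states: "The study foresees two groups (one of study and one of control) of 20 subjects each".
- **Imaging outcomes.** The MRI Data Processing section has its own rule for activity and connectivity, before and after treatment or between groups: linear mixed effect models, with no log step.
- **Sign of the imaging measures.** The Purpose of the Study section makes change in activation and connectivity the main aim, and the introduction says that "the individual structures of each network seem to be anti-correlated".

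**The concern.** A chi-square test on a two-row table has K − 1 degrees of freedom for K categories and looks for any difference in the distribution. A treatment effect on an ordered scale is usually a shift towards one end. Chi-square spreads its power over all patterns of difference, most of which are of no interest, while a rank test directs it at the shift. With only 20 per arm there is little power to give away, and because the rule extends to end of treatment it is an outcome test and not just a description of baseline balance.

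The log sentence raises a smaller question. It speaks of the data in general, while a change or a correlation can be zero or negative and then has no logarithm.

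**Working it through.** **Inputs from the protocol.** 20 per arm; significance level from "The level of statistical significance is established for an alpha <0.05", taken as two-sided because sidedness is not stated; chi-square for ordinal variables. **Assumed, because the protocol does not give them:** the number of categories, their distribution, and the common odds ratio.

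**1. The plan's own figure.** With d = 1.01 and "alpha and beta value of 0.05 and 0.8 respectively" (the 0.8 can only sensibly be read as power), the normal approximation gives

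n = 2(z₀.₉₇₅ + z₀.₈)² / d² = 2(1.960 + 0.842)² / 1.01² = 15.4, rounded up to 16.

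This matches "resulting in N=16 subjects per group". The t-test version gives 16.4, so 17. At 20 per arm, power for d = 1.01 is 0.89 (normal) or 0.88 (t). The sample size rests on a continuous imaging measure, so the ordinal rule does not affect it.

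**2. Building an ordinal effect.** Take five equally likely categories in one arm, with cumulative probabilities 0.2, 0.4, 0.6, 0.8 and odds 0.25, 0.667, 1.5, 4. Dividing each odds by 3 and converting back gives cumulative probabilities 0.077, 0.182, 0.333, 0.571. The other arm's category probabilities are then 0.077, 0.105, 0.152, 0.238, 0.429.

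**3. Power for a five-level item, 20 per arm** (6,000 simulated trials per setting):

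| Common odds ratio | Chi-square | Wilcoxon-Mann-Whitney |
|---|---|---|
| 1 (no effect) | 0.047 | 0.047 |
| 3 | 0.258 | 0.460 |
| 5 | 0.535 | 0.783 |

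The loss is 0.460 − 0.258 = 0.20 at an odds ratio of 3 and 0.783 − 0.535 = 0.25 at 5. Repeat simulations with five equal categories agree to within about 0.02.

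**4. Dependence on the number and spread of categories**, odds ratio 4 (5,000 trials for power, 8,000 for type I error):

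| Scale | Chi-square power | Rank-test power | Chi-square type I error |
|---|---|---|---|
| 3 equal | 0.52 | 0.62 | 0.051 |
| 4 equal | 0.47 | 0.64 | 0.052 |
| 5 equal | 0.43 | 0.66 | 0.045 |
| 5 skewed (two patterns) | 0.37, 0.29 | 0.62, 0.52 | 0.034, 0.029 |
| 7 equal | 0.32 | 0.66 | 0.038 |

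The loss runs from about 10 points (three categories) to 34 points (seven).

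**5. Expected counts.** With equal arms the mean expected count per cell is 20/K: 6.7 for K = 3, 5.0 for K = 4, 4.0 for K = 5, 2.9 for K = 7. Under no effect with equal categories, the usual guide (at most 20% of cells below 5) fails in 29% of simulated tables at K = 3, in 99.6% at K = 4, and in all of them at K = 5 and K = 7. The type I error column shows that this sparseness does not produce excess false positives.

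**6. The log.** A change score distributed symmetrically about zero has 50% of its values at or below zero. For connectivity values assumed normal with SD 0.2, the share at or below zero is 31% at mean 0.1, 6.7% at mean 0.3 and 0.6% at mean 0.5. A plain log cannot be taken of such values. It can be taken of positive measures such as GABA concentration or cerebral blood flow.

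**The case against.** **No outcome is labelled ordinal.** SF-36v2, McGill, Oswestry, BDI-II, HADS and BAQ could all be scored as numerical totals and go to ANOVA. The likeliest ordinal item is satisfaction with treatment, which is not among the stated aims and whose response format is not given. This stands, and it limits the reach of the point. The rule itself is nonetheless stated, and it is the weaker choice wherever it applies.

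**A reader might infer that chi-square is invalid at this sample size.** The protocol does not support that. Sparseness depends on a category count it never gives, the expected-count guide often holds with three categories and need not fail with two, and simulated type I error stays at or below about 5%. The cost is power.

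**A reader might also infer that the primary imaging outcome will be log-transformed, with negative values dropped or shifted.** The protocol does not say so. The log is only a possibility, no variable is named, and MRI Data Processing sends activity and connectivity to mixed models. It is true that the null hypothesis in Statistic Analysis does not expressly exclude imaging outcomes, so the scope of the log sentence is unclear; that warrants a clarification and no more. The anti-correlation remark in the introduction makes negative values plausible but does not show that they would be logged.

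**Finer choices may sit in a statistical analysis plan.** Connectivity scale, permutation checks and the role of the Shapiro test are matters of preference or of such a plan, and nothing here rests on them.

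**Conclusion.** The point holds for ordinal variables. The protocol fixes a test that ignores order, and at 20 per arm this costs roughly 10 to 34 percentage points of power against a rank test in the scenarios examined; for a five-level item it is about 26% v 46% at an odds ratio of 3 and 54% v 78% at 5. These sizes depend on assumed category counts, distributions and odds ratios, on a shift of proportional-odds form, and on a two-sided 5% level. False-positive risk is not raised, and neither the sample size nor the mixed-model analysis of the primary imaging outcome is affected. The unrestricted log sentence is a minor matter of wording. Overall this is a free improvement to a secondary part of the plan, not a threat to its main conclusion.

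**What to change.** In Statistic Analysis, replace the combined rule for categorical and ordinal variables with three parts:

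- Ordinal variables, at baseline and at end of treatment: Wilcoxon-Mann-Whitney, or a proportional-odds model where adjustment for age and gender is wanted.
- Nominal variables: chi-square.
- Nominal variables with small expected counts: Fisher's exact test.

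State also which questionnaires are analysed as numerical totals and which items, such as satisfaction, as ordinal.

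As a clarification, limit the optional log transformation to strictly positive variables, for example GABA concentration and cerebral blood flow, and say that activity and connectivity follow the mixed models in MRI Data Processing without it.

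The cost is a few sentences. No patients, visits or measurements are added, and all the methods are available in R, which the protocol already names.

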**MRI DATA PROCESSING**

The functional, structural and spectroscopic magnetic resonance data will be analyzed with dedicated software (AFNI, FSL, JMRUI) or specifically developed at ITAB, obtaining both individual and group functional activation and connectivity maps. Differences in activity and connectivity pre / post or between groups in the insula and other regions of interest will be evaluated through linear mixed effect models.

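### The end-of-treatment ANOVA between arms is not adjusted for the baseline scan value, and the protocol does not say whether it or the linear mixed model is primary

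*Protocol*

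**What the plan says.** All references are to the Protocol.

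- **STATISTIC ANALYSIS, hypothesis and test.** The null hypothesis is no difference between the two groups at the end of treatment. Numerical variables are compared by univariate ANOVA, mainly at baseline, and then "with the same method we will also analyze the data at the end of the treatment". The same sentence concedes that this method cannot isolate independent effects. A general statement says analyses are standardised by age and gender, without saying how this enters an ANOVA.
- **STATISTIC ANALYSIS, further models.** "ANCOVA will be used to explore in greater detail the treatment effect considering cofactors"; the cofactors are not named. Then: "Multivariate analysis will include the use of the best weighed model for confounding and interaction factors"; no criterion for best is given.
- **MRI DATA PROCESSING.** Pre/post or between-group differences in activity and connectivity in the insula and other "regions of interest will be evaluated through linear mixed effect models".
- **OUTCOMES.** The scans are taken at baseline, right after the first session, and at the end of the treatment period.
- **STATISTIC ANALYSIS, sample size.** The effect size, d = 1.01, comes from a "comparison of connectivity values between different populations". It was entered "together with an alpha and beta value of 0.05 and 0.8 respectively", "resulting in N=16 subjects per group". The randomisation section plans 20 per group.

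**The concern.** The protocol gives one between-arm hypothesis several analyses and ranks none of them as primary. The one tied most directly to the stated null hypothesis compares final values without the baseline value of the same measure. In a trial of 40 people that measure is likely to be the strongest available predictor. The protocol's own introduction describes resting-state signal properties as stable across sessions.

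Two things are at stake. The first is precision: variation between subjects that the baseline scan could explain stays in the error term. The second is pre-specification: with an end-value ANOVA, an ANCOVA, a best model and a mixed model all available for one question, the reader cannot tell in advance which result will count.

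**Working it through.** **Inputs.** From the protocol: d = 1.01; alpha 0.05; power 0.80 (the protocol labels 0.8 as beta, which can only sensibly mean power); 16 per group calculated; 20 per group planned; 1:1 allocation. Assumed: a two-sided test, since sidedness is not stated; baseline-to-end correlation r of 0.3, 0.5 or 0.7, since no value is given; and a smaller effect of d = 0.7 for comparison, because 1.01 is borrowed from a contrast between populations.

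**Step 1: the plan's own figure.** Two means, normal formula: n = 2(1.96 + 0.842)² / 1.01² = 15.4, rounded up to 16 per group. This reproduces the stated figure. The noncentral t needs 17; at n = 16 its power is 0.789. The sizing is therefore that of a two-group comparison with no allowance for a baseline covariate.

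**Step 2: effect of baseline adjustment.** Adjusting the end value for its baseline multiplies the error variance by 1 − r². The standardised effect becomes d / √(1 − r²), and the noncentrality at 20 per arm is d√(20/2) / √(1 − r²), with 37 degrees of freedom instead of 38.

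For d = 1.01 without baseline, the noncentrality is 1.01 × √10 = 3.194 and power is 0.875. For d = 0.7 it is 0.7 × √10 = 2.214 and power is 0.578.

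| r (assumed) | 1 − r² | Noncentrality, d = 1.01 | Power, d = 1.01 | Noncentrality, d = 0.7 | Power, d = 0.7 |
|---|---|---|---|---|---|
| no baseline | 1.00 | 3.194 | 0.875 | 2.214 | 0.578 |
| 0.3 | 0.91 | 3.348 | 0.903 | 2.320 | 0.618 |
| 0.5 | 0.75 | 3.688 | 0.949 | 2.556 | 0.702 |
| 0.7 | 0.51 | 4.472 | 0.992 | 3.100 | 0.855 |

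**Step 3: the same gain as sample size.** For d = 1.01 and 80% power by the normal formula, the need falls from 16 per arm to 15, 12 and 8 at r = 0.3, 0.5 and 0.7 (noncentral t: from 17 to 16, 13 and 9).

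**Step 4: the two sections side by side.** STATISTIC ANALYSIS sizes the trial on an fMRI effect, states the null hypothesis and names ANOVA for numerical variables. MRI DATA PROCESSING names mixed models for between-group differences in activity and connectivity. Both therefore cover the imaging contrast between arms at the end of treatment, and neither refers to the other.

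**Step 5: what an open choice could cost.** This is an illustration; the protocol does not say that anyone would choose this way. If the smaller p-value of the end-value ANOVA and the baseline-adjusted ANCOVA were reported, simulation with 20 per arm and no true effect gives a type I error of about 6% at r = 0.3 and 8 to 9% at r = 0.7, against a nominal 5%.

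**The case against.** The strongest reply is that the specific section governs imaging and the general one covers demographics and questionnaires. The MRI section deals only with imaging. The statistics section speaks of percentages, chi-square tests and numerical variables at large. On that reading a mixed model over the scans could already use baseline, and the precision loss would not arise for the fMRI outcome. This stands as a possible reading, and it is why the loss must be stated conditionally. It does not remove the conflict, because the statistics section also carries the fMRI sample size and the trial's null hypothesis.

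Other points that stand:

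- A reader might infer that the test is wholly unadjusted. The text does not support that: age and gender are to be standardised for. What is missing is the baseline value.
- A reader might infer that the best model will be picked from the data. That is only an inference from a phrase with no criterion; the protocol describes no selection procedure.
- A reader might infer bias from chance baseline imbalance. Under randomisation the end-value comparison is unbiased, and its standard error already allows for such imbalance.
- On the plan's own d = 1.01, power exceeds 80% without baseline adjustment.
- Covariate lists and model terms are commonly left to an SAP, and their absence is not the point here. The point is that two sections of the protocol name different analyses for one contrast, so an SAP would have to choose between them.

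The purpose section also frames the main aim as before-to-after change and lists the sham comparison among secondary goals. Naming a between-arm model does not by itself settle that.

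**Conclusion.** The point holds as a matter of efficiency and pre-specification. It does not make the trial's comparison invalid. If the statistics section governs, the between-arm test discards a baseline scan that is already collected. The cost is modest on the plan's effect size (about 3, 7 or 12 percentage points of power at r = 0.3, 0.5 or 0.7) and larger if the true effect is smaller (about 4, 12 or 28 points at d = 0.7). These figures rest on r and d = 0.7, which are assumptions, and on a two-sided test. If the MRI section governs and its model includes the baseline scan with arm-by-time terms, the precision loss disappears; the protocol states neither. Under either reading the primary between-arm analysis is not identified, and this part does not depend on any assumed figure. The change is worth making and easy to make.

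**What to change.** Amend STATISTIC ANALYSIS and MRI DATA PROCESSING so that both name the same primary between-arm analysis, tested by the arm contrast at end of treatment. Either of these would do:

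1. ANCOVA of the end-of-treatment value with arm, the baseline value of the same measure, age and gender as fixed covariates. The arm estimate is the same whether the response is the end value or the change from baseline, so it also serves the before-to-after framing when arms are compared.
2. The linear mixed model over the three scans with a random subject effect, arm-by-time terms, baseline means constrained equal across arms, and age and gender fixed.

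Baseline should enter as a response or as a covariate, not both. Label the end-value ANOVA and the best-model step as sensitivity or exploratory.

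Cost: analysis wording and one or two degrees of freedom. No new data are needed.

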
MATERIALS AND METHODS

PURPOSE OF THE STUDY

The main aim of the present randomized controlled two-arm and single-blind study is to evaluate the change in activation and connectivity of the anterior cortex of the insula and the medial prefrontal cortex between before and after the period of manual treatment with osteopathic modality. Secondary goals are:

I) to monitor the differences of activity and FC of the SN between the study group and the sham control;

II) to monitor the intra-group differences and the intergroup of activities and of the CF of the SN immediately after the first treatment;

III) to monitor the differences in activity of intra-group and inter-group RSN during the treatment period;

IV) to monitor the differences in the IA and EA both within and between groups;

V) to evaluate the DTI structural differences;

VI) to evaluate differences in terms of GABA concentration in the anterior insula by means of

MRS

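### One alpha of 0.05 covers every comparison, and within-arm changes stand level with the randomised contrast, so secondary results can be declared significant without limit (minor)

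*Protocol*

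**What the plan says.** Protocol, Statistic Analysis: the significance rule is "The level of statistical significance is established for an alpha <0.05", attached to no outcome. The only hypothesis is "The hypothesis H0 (null hypothesis) is the non-difference between the two groups at the end of the treatment". The tests are described for variables in general: "the univariate analysis foresees the use of the analysis of the variance (ANOVA) for the comparison of the numerical variables", with chi-square for categorical or ordinal variables. The same methods serve the baseline and the end-of-treatment data.

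Protocol, Purpose of the Study: a main aim (before/after change in activation and connectivity of the anterior insula and medial prefrontal cortex) is followed by six goals labelled secondary. Goal II is "to monitor the intra-group differences and the intergroup of activities and of the CF of the SN immediately after the first treatment". Goals III and IV also ask for within-group and between-group differences. Goal I is between groups only. Goals V and VI do not say.

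Protocol, MRI Data Processing: linear mixed effect models will evaluate "Differences in activity and connectivity pre / post or between groups in the insula and other regions of interest".

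Protocol, Outcomes: seven instruments are collected at the end of the study (SF-36v2, satisfaction, McGill, Oswestry, BAQ, BDI-II, HADS). None is assigned to a numbered goal.

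**The concern.** Two features of the text combine. First, the 0.05 rule is general, so a secondary brain measure, an extra region or a questionnaire score can be called significant on the same terms as the stated null hypothesis. Second, within-arm change is offered as an alternative to the randomised comparison. A significant pre/post change in the osteopathic arm beside a non-significant one in sham could then be presented as a treatment effect, although any change common to both arms (natural course, touch, repeat scanning) can produce that pattern.

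The secondary label only partly settles the matter. The main aim is worded as a before/after change, while the null hypothesis is a between-group contrast that overlaps secondary goal I. The labels alone therefore do not show which test owns the 0.05.

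**Working it through.** **The plan's own figure.** The inputs are "indicate relatively high values (Cohen ‘s d= 1.01" and "alpha and beta value of 0.05 and 0.8 respectively". The 0.8 makes sense only as power. The normal formula for two means, two-sided, gives n = 2 × ((1.960 + 0.842) / 1.01)² = 15.39, rounded up to 16. This matches "resulting in N=16 subjects per group". The calculation thus assumes a single between-group test at 0.05. The planned 20 per arm gives about 88% power for that test (noncentral t).

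**False positives across secondary tests.** The protocol gives neither the number of tests nor their correlation, so both are assumptions. Three counts of between-arm tests are used:

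- 6: one per goal.
- 9: goal I activity and connectivity (2), goal II the same after session 1 (2), III (1), IV interoceptive and exteroceptive (2), V (1), VI (1).
- 24: those nine plus 15 end-of-study scores (8 SF-36 domains, 2 HADS scales, and one each for satisfaction, McGill, Oswestry, BAQ and BDI-II).

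For m independent tests the family-wise rate is 1 − 0.95^m. For example, 1 − 0.95⁶ = 0.265. For equally correlated two-sided z-tests the rate comes from integrating over a common factor: 1 − ∫ φ(x) [Φ((1.96 − √ρ x)/√(1−ρ)) − Φ((−1.96 − √ρ x)/√(1−ρ))]^m dx.

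| Tests | ρ = 0 | ρ = 0.5 | ρ = 0.8 |
|---|---|---|---|
| 6 | 26.5% | 20.7% | 13.9% |
| 9 | 37.0% | 26.9% | 16.5% |
| 24 | 70.8% | 45.8% | 23.8% |

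Within-arm tests, per-session questionnaires and extra regions are not counted.

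**Discordant within-arm results.** Suppose both arms truly change by the same d, in SDs of the change score. With 20 per arm, let q be the power of a two-sided one-sample t-test (19 degrees of freedom, noncentrality d√20). The arms are independent, so the probability of significance in the osteopathic arm and not in sham is q(1 − q).

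| d (assumed) | q | q(1 − q) |
|---|---|---|
| 0.2 | 0.136 | 12% |
| 0.3 | 0.247 | 19% |
| 0.45 | 0.480 | 25% |
| 0.6 | 0.721 | 20% |
| 0.8 | 0.924 | 7% |
| 1.0 | 0.989 | 1% |

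Since q(1 − q) cannot exceed 0.25, the value at 0.45 SD is the peak of the range and not a typical figure.

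**Why a blanket correction is not the remedy.** Bonferroni over six tests gives 0.05 / 6 = 0.0083. At d = 1.01 and 20 per arm, power would fall from about 88% to about 66%, and 80% power would need about 26 per arm. Limiting the claim avoids this loss.

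**The case against.** The strongest reply is that multiplicity handling for secondary and questionnaire outcomes normally belongs in the statistical analysis plan, which is not shown, and that unadjusted secondary tests are usually read as supportive. This stands: the absence of a correction procedure is not itself an error here.

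Other parts of the reply also stand:

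- A reader might infer that the protocol has no hierarchy at all. It does rank a main aim above labelled secondary goals, and it states one null hypothesis.
- A reader might infer that every questionnaire score is tested at 0.05. No questionnaire is named in the statistics section; this is only the natural reading of the general ANOVA wording. The eight SF-36 and two HADS tests are assumed, and satisfaction is collected to assess acceptance of treatment.
- A reader might infer that a false secondary finding is more likely than not. At correlation 0.5 the rates are 21%, 27% and 46%, all below one half.
- Nine is not a minimum count, and its two goal I tests overlap the stated null hypothesis. Without them, seven independent tests give 1 − 0.95⁷ = 30%.
- Within-arm comparison is written only for goals II to IV, each of which also asks for the between-arm comparison. Ignoring the latter would be misreporting, not something the plan requires.

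The reply does not remove what the protocol positively states: a significance rule with no limit on its scope, and an MRI analysis sentence that joins pre/post and between-group differences with an or, over open regions.

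**Conclusion.** The point holds as a minor one. The protocol's wording lets a within-arm change or any secondary result be declared significant on the same footing as the randomised comparison. With no treatment effect, the chance of at least one false significant secondary result is 14% to 27% for six tests, 17% to 37% for nine and 24% to 71% for 24, over correlations from 0.8 down to 0. For a common change of 0.2 to 1.0 SD in both arms, the misleading one-arm pattern arises in 1% to 25% of trials. These figures rest on assumed test counts, equal correlations and two-sided testing (sidedness is not stated). The 24-test figure also rests on the inferred testing of questionnaires. They show a substantial risk, not a probable one, and they do not bear on the validity of the main between-arm test.

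**What to change.** - **Statistic Analysis:** tie the 0.05 rule to the between-arm null hypothesis for the main-aim regions, including the part of goal I that coincides with it, so that the randomised comparison is not demoted. State that the remaining secondary goals, the questionnaires and any other region are supportive, reported as between-arm estimates with 95% confidence intervals.
- **Purpose of the Study (goals II to IV) and MRI Data Processing:** base conclusions about treatment effect on the between-arm contrast from the mixed model (arm by time, or baseline-adjusted). Keep within-arm changes as description.

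The cost is wording in three sections. No patients or scans are added, and the main test keeps its alpha and sample size. The small downside is that an isolated secondary result with p below 0.05 can no longer be claimed as confirmed.
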